## Abstract

**Aim:**

To determine the effectiveness of a hydrophobic dressing (Cutimed Sorbact^®^) against a silver dressing (Aquacel^®^ Ag Extra) in the level of colonization of chronic venous leg ulcers. The secondary endpoints are health‐related quality of life, level of pain, and time to complete healing.

**Design:**

Open randomized controlled trial, with blinded endpoint.

**Methods:**

Patients with chronic venous leg ulcers with signs of critical colonization will be randomized in a concealed sequence using computer software to receive one of the alternative dressings. A total of 204 participants recruited in Primary Health Care and nursing homes will be necessary to assure statistical power. Measures will include sociodemographic variables, wound‐related variables (area, exudate, and time to healing), level of pain, adverse effects, and health‐related quality of life. Smear samples will be collected from the ulcers and will be subject to DNA‐typing technique through polymerase chain reaction to obtain the level of colony‐forming units. Measures will be collected at baseline, 4, 8, and 12 weeks.

**Discussion:**

Elevated levels of microorganisms prevent wound healing and favour its chronification. The main target when colonization is present is to reduce the bacterial load to levels that promote immune system mobilization. Hydrophobic dressings prevent the formation of biofilm in the wound by means of physical effect, so that the possibility of antimicrobial resistance is significantly reduced.

**Impact:**

Current evidence about the effectiveness of dressings to minimize venous leg ulcers colonization is very limited. Previous studies have important methodological flaws. This study will permit to obtain the effectiveness of hydrophobic dressings against silver dressings with a robust design based on conditions of routine clinical practice in Primary Health Care and nursing homes.

## INTRODUCTION

1

Chronic wounds of torpid evolution are currently a great challenge for health services worldwide. In Europe, they can eventually lead to 2–4% of health expenditure (Posnett, Gottrup, Lundgren, & Saal, 2009). Particularly, venous ulcers are estimated that would affect at least 1% of adult population throughout their lifetime. Studies have determined venous ulcer frequency around 0.2–1.1% (Graham, Harrison, Nelson, Lorimer, & Fisher, 2003), thought this figure can rise up to 4% in people over 65 years old (Pugliese, 2016).

Clinical nursing has a key role in the detection, diagnosis, treatment, and tracking of venous leg ulcers. It is important to identify the different types of wounds and their characteristics that nurses can find in their clinical practice, and the appropriate treatments that can be carried on. Furthermore, the healing of these chronic wounds depends on the choice of the most suitable designed dressing. Most of times, this decision relies on the clinical nurse's judgment about the venous ulcer evolution (Davies, Turton, Woolfrey, Elley, & Taylor, 2005).

### Background

1.1

More than 80% of venous leg ulcers may be colonized or infected by bacteria (O’Meara et al., 2014). One of the leading causes of delay in the healing is the presence of pathogenic bioburden. In fact, bacterial biofilms (exopolysaccharides extracellular matrix which provides structural bacterial defence) over the wound have been associated with chronic wound interference recovery (Clinton & Carter, 2015; Gompelman, van Asten, & Peters, 2016; Hurlow et al., 2015). Moreover, biofilm provides a key resistance to local and systemic antibiotic treatments, especially in the case of venous ulcers (Bianchi et al., 2016). Major representative strains are *Staphylococcus aureus* and *Pseudomonas aeruginosa*, while it can be also found in anaerobic microorganisms (*Peptostreptococcus* species and gram‐negative *Bacillus*), *Enterobacteria,* or group A *Streptococcus* (Etchebarne et al., 2017).

The presence of colonization or infection in chronic wounds produces a direct effect in their healing and recovery when colony‐forming units (CFUs) exceed 10^5^ per tissue gram. Thus, wound colonization by pathogenic bacteria promotes its chronification. Furthermore, pathogenic bacteria can also generates intra‐wound synergistic effects with other non‐pathogenic microorganisms increasing their action (Rahim et al., 2017).

This problem has been usually addressed by using local dressings, with the aim to reduce the total wound bacterial load. Although the most common therapeutic strategy is the use of silver dressings due to their antimicrobial effect, there is a lack of evidence about their effectiveness in venous ulcers (O’Meara et al., 2014). Moreover, there is some uncertainty over adverse effects derived from systemic absorption of silver molecules, in addition to generate silver resistance in many bacteria strains (Maillard & Hartemann, 2013; Mijnendonckx, Leys, Mahillon, Silver, & Van Houdt, 2013; Percival et al., 2008). Additionally, these inconveniences can involve an elevated cost when long‐term treatments are needed.

A novel approach to deal with the problem of chronic wound colonization is the use of hydrophobic dressings. It has been extensively addressed that when two hydrophobic molecules contact each other, they increase their molecular entropy by hydrophobic interactions to finally expelling residual water molecules (Curtis, Steinbrecher, Heinemann, Blanch, & Prausnitz, 2002). Thus, hydrophobic surface microorganisms present a high probability to join to hydrophobic dressings, allowing hydrophilic bacteria to rest at the wound bed to promote the healing. In vitro experiments have also showed that most pathogenic microorganisms present high hydrophobic membrane molecules (Ljungh, Yanagisawa, & Wadström, 2006).

Hydrophobic mechanism is neither based on active absorption of exudate nor placing chemical agents on the surface of the ulcer. In fact, the presence of dialkylcarbamoyl chloride (DACC)‐coated dressings attract hydrophobic fungus and bacteria, avoiding the formation of biofilm in the wound (Derbyshire, 2010). In this sense, antimicrobial properties of hydrophobic dressings are based on physical effects instead of chemical effects. Consequently, the possibility to generate antimicrobial resistance is significantly reduced (Ljungh et al., 2006). Furthermore, it has been analysed how local antiseptic administration could affect to the expression of the hydrophobic bacterial membrane. Thus, the use of eutectic mixture of local anaesthetics (EMLA) or glycol‐carbohydrates modified polymers (Askina^®^) can interfere hydrophobicity, whereas this property is not affected by other products commonly used in the care of wounds, such as povidone‐iodine or saline solutions (Ljungh et al., 2006).

Although there are some preliminary studies which compare high hydrophobic dressings versus silver dressings, they have been carried out with reduced samples in pilot studies (Mosti, Magliaro, Mattaliano, Picerni, & Angelotti, 2015; Mussi & Salvioli, 2004). Furthermore, the study population in these studies did not include patients in home or ambulatory care, the most frequent clinical settings with a high demand for this type of wounds. In addition, the trials carried out have evaluated the results throughout short follow‐up periods. All these issues limit the available evidence on hydrophobic dressings, as it has been stated in a recent systematic review (Totty et al., 2017).

## THE STUDY

2

### Aim

2.1

The main aim of the study is to determine the effectiveness of a hydrophobic dressing (Cutimed Sorbact^®^) against a silver dressing (Aquacel^®^ Ag Extra) in the level of colonization of chronic venous leg ulcers.

The secondary aims will be to analyse the effect of Cutimed Sorbact^®^ versus Aquacel^®^ Ag Extra on total healing, the proportion of wound reduction, time of recovery, level of pain during recovery, and health‐related quality of life. In addition, the safety of Cutimed Sorbact^®^ will be evaluated.

The null hypothesis is that there is no difference in the level of bacterial colonization at 12 weeks of follow‐up in chronic ulcers treated with Cutimed Sorbact^®^ versus those treated with Aquacel^®^ Ag Extra.

### Methods

2.2

#### Design

2.2.1

An open, randomized, controlled trial with blinded evaluators will be carried out.

#### Sample

2.2.2

Assuming a 95% confidence level and 80% statistical power, 186 participants would be necessary (93 for each study arm) to detect a 20% load bacteria reduction (Mosti et al., 2015). This sample will be increased up to 204 participants to cover any possible patient dropouts.

#### Allocation

2.2.3

Inclusion of participants will be randomized in a concealed sequence to participants, clinical nurses, and investigators. Once a participant meets the inclusion criteria, collaborative investigators will know by means of a telephone call the study group assigned according to the random sequence. The random sequence will be generated by a computerized system. Although the study groups are not blinded for patients and nurses, the members of the team who will carry out the analyses will be blinded to the allocation groups.

#### Participants

2.2.4

##### Inclusion criteria

The study will be developed in adult patients who are attended in health centres or nursing homes belonging to the District of Primary Health Care of Málaga (Spain), who present a chronic venous vascular ulcer located in their lower limbs with signs of critical colonization, according to the criteria of Lazareth and Moore (Lazareth et al., 2007; Moore, 2013). These criteria imply the presence of at least three of the following: (a) Severe pain during dressing change; (b) Perilesional oedema; (c) Local oedema; (d) Unpleasant smell; and (e) Abundant pus.

In case of fulfilling the mentioned criteria, an exudate sample will be collected from the wound by the primary healthcare nurse. Ulcer infection would be assumed in case of a level of microorganisms per tissue gram or microbial counting over 10^5^ CFUs per microlitre (μL) (Pugliese, 2016).

##### Exclusion criteria

The exclusion criteria will be: people younger than 18 years old, venous ulcer that does not meet Lazareth and Moore criteria, arterial ulcers, participants with diabetes and without pedis pulse, people who are immunosuppressed, patient with rheumatoid arthritis in the acute phase, patients with dermatitis prior to the appearance of the ulcer, and patients with neuropathy or lack of sensitivity of any aetiology.

#### Data collection

2.2.5

Patients will be recruited by clinical nurses in health centres and nursing homes belonging to the District of Primary Health Care of Málaga (Spain). Following obtaining the patients’ informed consent, sociodemographic variables (age, gender), wound location and characteristics, and current treatment will be collected at baseline, together with the endpoints by the nurse who usually give care to the patient. This will reinforce the patient adherence to the study.

##### Primary endpoint

Level of colonization: it will be evaluated by quantitative real‐time polymerase chain reaction (qPCR) identification technique and quantified in CFUs and in nanograms (ng) of bacterial deoxyribonucleic acid (DNA) per μl of vascular ulcer exudate.

Two samples per wound (to have a reserve sample in case of possible contamination) will be collected by cotton swab directly from the wound bed. The samples will be collected before cleaning the wound to obtain a reliable microorganisms’ concentration. Swab tip will be rotated in a 1 cm^2^ wound surrounding area for 5 s. Next, cotton swabs will be placed in a sterile container at 4 ºC (Pugliese, 2016) until the process of qPCR.

Then, to determinate the total microorganisms’ quantity, samples will be subjected to a thermal shock, which consists in freezing them at −80ºC for 5 min, followed by heating samples at 95ºC for additional 5 min. With this procedure, gram‐positive and gram‐negative bacteria will be efficiently lysed. After spin centrifugation, DNA strands will be extracted for the following steps. The total DNA quantity of the isolated DNA will be measured using NanoDrop^TM^ spectrophotometer. Microorganisms will be quantitative determined by qPCR (referred to number of DNA copies amplified by this technique) (Rhoads, Wolcott, Sun, & Dowd, 2012).

Fast EvaGreen^®^ qPCR Master Mix (2X) kit will be used for qPCR amplification reactions, including specific primers usually present in vascular ulcers (Table 1; Etchebarne et al., 2017). Serial dilution will be performed from purified genomic DNA to generate a concentration calibration curve to compare data obtained from samples. From there, it will be possible to detect not only the presence of microbial species but also the quantitative determination of variation in these stains in samples of the same patient, as well as comparing treatments. Results will be standardized to CFUs per μL of exudate.

**Table 1 jan14412-tbl-0001:** Pathogen list usually founded and detected in vascular ulcers (Majewski et al., 1995) in addition to multi‐resistant pathogens (Moore et al., 2010)

Microorganism	Feature
*Staphylococcus aureus*	Commonly found on vascular ulcers
*Corynebacterium striatum*	
*Pseudomonas aeruginosa*	
*Helcococcus kunzii*	
*Proteus mirabilis*	
*Finegoldia magna*	
*Escherichia coli*	
*Staphylococcus aureus* methicillin/oxacillin resistant	Multi‐resistant pathogen described on vascular ulcers
*Acinetobacter baumannii* MDR (Imipenem resistant)	
*Klebsiella pneumoniae* producing BLEE	
*Enterococcus* vancomycin resistant	
*Enterobacteria* producing carbapenem	
*Pseudomonas aeruginosa* MDR producing BLEE or carbapenem, or piperacillin resistant	

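### The primary endpoint measures total bacterial DNA but is labelled CFUs, so a lower value does not by itself show lower viable colonization, and the error may differ between arms

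*Protocol article*

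**What the plan says.** **Measurement.** The Primary endpoint section (2.2.5) takes a swab from the wound bed before the wound is cleaned. The aim is the total quantity of microorganisms, and "samples will be subjected to a thermal shock", a freeze at −80 ºC followed by heating to 95 ºC, which is meant to lyse both gram-positive and gram-negative cells. Then: "Microorganisms will be quantitative determined by qPCR (referred to number of DNA copies amplified by this technique". The calibration curve is a serial dilution of purified genomic DNA.

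**Unit.** The same section gives the endpoint in CFUs and in nanograms of bacterial DNA per µl, and ends by standardizing results to CFUs per µl of exudate. Data analysis (2.2.7) makes the CFU number the dependent variable for testing the null hypothesis. Background (1.1) and Inclusion criteria (2.2.4) both interpret load against a threshold of 10^5 CFUs.

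**Mechanisms.** Background says "the most common therapeutic strategy is the use of silver dressings due to their antimicrobial effect", and for the test dressing that "antimicrobial properties of hydrophobic dressings are based on physical effects instead of chemical effects". The Discussion (3) contrasts a chemical with a physical approach and describes the aim of drawing bacteria into the dressing.

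**The concern.** A colony-forming unit is a cell or clump able to grow. A DNA copy may come from a living or a dead cell, and nothing in the described workflow separates them or converts copies to colonies. The unit is therefore wrong as written.

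Were the dead-cell share similar in both arms, this would mostly be a labelling matter. But the article gives the two dressings different modes of action. One acts chemically on bacteria, which may leave their DNA on the wound bed. The other binds bacteria and leaves with them at the dressing change, and the removed dressing is not sampled. A difference in measured load could then partly reflect dead-cell DNA rather than better bacterial control. The Discussion expects a finding of reduced colonization to translate into shorter healing times, so the reading of the endpoint matters.

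**Working it through.** **Step 1: does the described assay yield CFUs?**

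| Step in the Primary endpoint section | What it yields |
|---|---|
| Freeze-heat shock of the whole sample | DNA of all cells, living or dead |
| qPCR | Number of DNA copies |
| Curve from purified genomic DNA | Copies or nanograms of DNA |
| Viability step, culture, or copies-to-colonies conversion | None described |
| Reported unit | CFUs per µl |

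Every described step yields a DNA quantity. Only the label is CFU.

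**Step 2: which way could the error run?** Dead-cell DNA can only add to the measured load. On the article's own account of the mechanisms, it may add more where bacteria are acted on chemically in place than where they leave with the dressing. The direction is plausible, not demonstrated. Randomization and blinded analysis do not remove it, because it arises in the measurement.

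**Step 3: what limits it?** The Intervention section (2.2.6) washes the wound with saline and considers debridement, at appointments no more than 72 hours apart. Over 12 weeks that is 84 days / 3 days = 28 intervals at least. The week-12 swab, taken before that visit's wash, should mainly reflect what has built up since the previous one.

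**Step 4: can a size be given?** The only design figure is in the Sample section: "186 participants would be necessary (93 for each study arm", "to detect a 20% load bacteria reduction", at 95% confidence and 80% power. No SD or arm-level rate is stated, so 93 cannot be reproduced from the stated inputs. If the 20% is read as a mean difference of 0.20 (an assumption), the implied SD is 0.20 × √(93/2) / (1.960 + 0.842) = 0.487, and the standard error of the difference is 0.487 × √(2/93) = 0.0714.

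Two illustrations follow. Both assume that the dressings reduce viable bacteria equally, silver only by killing and the hydrophobic dressing only by removal, and that a share f of killed-cell DNA remains at sampling. No value of f is in the documents.

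*Illustration A, proportional scale.* With an assumed viable reduction R = 60%, the spurious gap is R × f. The chance of a significant result favouring the hydrophobic dressing is Φ(gap/0.0714 − 1.96).

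| f | Gap | Chance |
|---|---|---|
| 0 | 0 | 2.5% |
| 10% | 0.06 | 13% |
| 25% | 0.15 | 56% |
| 33% | 0.20 | 80% |

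*Illustration B, log scale.* Assume a 1 log10 viable reduction and an SD of 1 log10. The measured silver load is 0.1 + 0.9f of baseline, against 0.1 in the other arm. At f = 10% it is 0.19, a gap of log10(0.19/0.10) = 0.279. With standard error √(2/93) = 0.147, z = 1.90 and the chance is about 48%. At f = 30% the load is 0.37, the gap 0.568, z = 3.87 and the chance about 97%.

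At the same f = 10% the two models give 13% and 48%, and neither models the repeated washing. They show that the error could matter if retention were substantial. They do not estimate it.

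**The case against.** The case against a strong claim is good, and much of it stands.

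- **The bias is not established.** A reader might infer that dead cells inflate the silver arm only and that the trial is biased against its control. The documents do not support this. They do not say that silver-killed cells stay on the wound bed with amplifiable DNA, or that the silver dressing carries nothing away. Both dressings are removed at each change, and bacteria can die in both arms. What stands is that dead-cell DNA may add more in the silver arm.
- **The error rates are driven by assumptions.** A reader might take the 48% and 97% above as the trial's false-positive risk, or set them against 5%. Reduction, retention and SD are all assumed. The right no-bias comparator for a result favouring one particular dressing is 2.5%.
- **The article partly discloses what it measures.** It states that qPCR refers to DNA copies and also lists nanograms of bacterial DNA. A conversion to CFUs might sit in the full protocol, which is not shown. This narrows the point but does not remove it: the workflow is given in detail, and the hypothesis test uses the CFU label rather than the DNA unit.
- **Clinical signs are a poor arbiter.** Making a colonization claim conditional on the inclusion signs or Resvech 2.0 would put an open-label filter on a laboratory result. Allocation (2.2.3) leaves nurses and patients unblinded, and Data collection (2.2.5) has the usual nurse record the endpoints.

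**Conclusion.** The point holds in a limited form. As described, the primary endpoint is total bacterial DNA, and calling it CFUs is wrong. A significant difference would show a lower DNA load, not by itself fewer viable bacteria. Error favouring the hydrophobic dressing is plausible from the article's own account of the two mechanisms, but its presence is unproven. Its size cannot be derived from the documents: the illustrations run from no effect at zero retention to a gap as large as the 20% design effect at 33% retention with a 60% viable reduction, before any allowance for washing. The conclusion about the unit rests only on the described workflow and would change if the full laboratory protocol contained a viability step or a validated conversion. The sample size of 93 per arm is not challenged here.

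**What to change.** 1. In Primary endpoint and Data analysis, define the outcome and the dependent variable as bacterial DNA load (log10 genome copies per µl, or nanograms of bacterial DNA per µl), and choose one of the two. Word the null hypothesis and the target reduction in the Sample section to match.
2. Drop the CFU label, and do not read the qPCR value against the 10^5 CFU threshold.
3. Add a sentence such as: *The assay counts DNA from viable and non-viable bacteria. Residual dead-cell DNA may differ between dressings, so a lower DNA load is not by itself evidence of lower viable colonization.*
4. Interpret the result alongside outcomes already collected (planimetric wound area, healing, Resvech 2.0) as supportive evidence, not as a condition for the claim.

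This needs no new visit, sample or participant. The cost is a more modest primary claim. A viability dye before lysis would address the question more directly but is an extra laboratory procedure. Using the reserve swab would give up the contamination backup for which it is collected. Neither is needed to correct the unit and the claim.

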##### Secondary outcome measures

Wound size will be evaluated by planimetry using PictZar^®^ 7.6.1 software (Wendelken et al., 2011). Photos will be taken from affected area completely in parallel with respect to the ulcer and the photo will have to include a calibrated rule of 3 cm (standardized procedure according to PictZar^®^ planimetry). The characteristics and clinical evolution of the wound will be evaluated using the Resvech 2.0 scale (Restrepo‐Medrano & Verdú Soriano, 2011).

Healing time will be measured by the number of days until complete healing. This outcome will be complied if re‐epithelialization of the skin is confirmed in two consecutive visits across 2 weeks. Pain will be measured using the Numerical Rating Scale (NRS).

Health‐related quality of life will be measured by means of the Charing Cross Venous Ulcer Questionnaire (CCVUQ) (González de la Torre, Quintana‐Lorenzo, Perdomo‐Pérez, & Verdú, 2017; González‐Consuegra & Verdú, 2010). Adverse events related to the treatment will be collected both by nurses and patients. Follow‐up will be carried out at 4, 8, and 12 weeks, except the quality of life, which will be only evaluated at baseline and 12 weeks. Adherence to the treatment will be checked with the nurse and with the evaluation of consumed dressings.

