#### Intervention

2.2.6

Following the obtention of the baseline data, the nurse who usually gives care to the patient will proceed to cure the venous ulcer using a standardized procedure. They will wash the area with saline solution and evaluate if mechanical debridement is necessary. Following, they will apply Cutimed Sorbact^®^ dressing (intervention) or Aquacel^®^ Ag Extra (control) dressings in the wound. Finally, they will cover the wound with a secondary gauze dressing and a double compression bandage. Patient's appointments will not extend beyond 72 hr, although depending on the level of exudate and the status of the wound, the nurse may decide to shorten this interval.

Dropout criteria are as follows: (a) Local or systemic clinical deterioration that indicates that continuation at the study is not appropriate; (b) Lack of patient's concordance; (c) Withdrawal of patient consent; and (d) Complete healing before week 12. The data collection period comprehends from May 2012 to December 2020.

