#### Data analysis

2.2.7

Data analysis will include descriptive statistics and exploratory analysis to determine the normality of the distributions and to check the range of data values. Bivariant analysis will be performed by chi‐square test, Student *t* test, Mann–Whitney U, Wilcoxon W, ANOVA, and Kruskal–Wallis test, depending on the normality of the distributions, type of variable analysed, and their homoscedasticity, which will be tested by the Levene's test. Intra‐group analysis will be performed by general linear models, with the corresponding corrections in multiple comparisons by Bonferroni test. To test the null hypothesis (inter‐group analysis), lineal generalized models will be developed in repeated measures, taking on consideration CFUs number as dependent variable as well as control or experimental designation group as a factor. Even if basal differences are significative, they will be attached as adjustment factor, following Mallinckrodt and Lipkovich recommendations (Mallinckrodt, Lipkovich, & Lipkovich, 2016). Sphericity will be tested using Mauchly test, Greenhouse‐Geisser test, or Huynh‐Feldt test in case of no setting.

All analyses will be performed by an intention‐to‐treat approach. To this purpose, missing data will be calculated by multiple imputation methods.

All the analyses will be performed in a blinded way.

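### Time to healing will be censored for ulcers still open at week 12, but the stated methods include none for censored times, and healing itself is listed as a dropout

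*Protocol article*

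**What the plan says.** The Abstract names time to complete healing as a secondary endpoint, and the Aim section lists both total healing and time of recovery.

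- **Scale** (Secondary outcome measures): "Healing time will be measured by the number of days until complete healing".
- **Event definition** (same section): "This outcome will be complied if re‐epithelialization of the skin is confirmed in two consecutive visits across 2 weeks".
- **Assessments** (same section): "Follow‐up will be carried out at 4, 8, and 12 weeks".
- **Care visits** (Intervention): "Patient's appointments will not extend beyond 72 hr".
- **Exit** (Intervention): the dropout criteria are deterioration, lack of concordance, withdrawal of consent and, fourth, "Complete healing before week 12".
- **Tests** (Data analysis): chi-square, Student t, Mann–Whitney, Wilcoxon, ANOVA and Kruskal–Wallis, chosen "depending on the normality of the distributions, type of variable analysed, and their homoscedasticity". General linear models serve within-group comparisons. A repeated-measures model with CFU count as the dependent variable serves the null hypothesis.
- **Population and missing data** (Data analysis): all analyses are by intention to treat, with multiple imputation for missing data.

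**The concern.** A healing time in days exists only for ulcers that heal under observation. For the rest, all that is known is that the time exceeds the last assessment. The rule for choosing a test looks at normality, variable type and equal variances, and does not mention censoring.

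If healing days are put through a t test or ANOVA, open ulcers must either be left out or be given an imputed healing day. Leaving them out selects patients on the outcome. Imputing treats a censored time as an absent one. Listing healing among the dropouts adds a second risk: a patient who reached the endpoint may be coded as lost.

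At stake is whether the comparison on this endpoint uses all randomised patients, and whether a real difference in healing would show.

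**Working it through.** **1. The plan's own figure.** The sample size (93 per arm, 186 in total, raised to 204, so 102 per arm) is for bacterial load. No figure is given for healing time, so there is none to reproduce. The healing rates below are assumptions. The tests are two-sided at 0.05, also an assumption because the sidedness is not stated.

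**2. Power at 30% v 50% healed by day 84.** Take 102 per arm, constant hazards and no earlier loss.

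- Hazard ratio = ln(0.5)/ln(0.7) = 0.693/0.357 = 1.94. Expected healings = 102 × (0.3 + 0.5) = 81.6, so 60% of ulcers are still open.
- Log-rank: z = √(81.6/4) × ln(1.94) − 1.96 = 4.52 × 0.664 − 1.96 = 1.04, power 85%. Simulation gives 83–85%.
- Chi-square on healed or not: SE under the null = √(2 × 0.4 × 0.6/102) = 0.0686; SE under the alternative = √((0.21 + 0.25)/102) = 0.0672. z = (0.20 − 1.96 × 0.0686)/0.0672 = 0.98, power about 83%.
- Healed patients only: the mean of an exponential time truncated at day 84 is 1/λ − 84(1 − p)/p. This gives 235.5 − 196.0 = 39.5 days and 121.2 − 84.0 = 37.2 days. The arms differ by 2.3 days, although the untruncated means differ by 114 days. With an SD of about 24 days and 30.6 and 51 healed patients, SE = 24 × √(1/30.6 + 1/51) = 5.5 days, and power is about 7%.

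Simulated power for two pairs of rates:

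| Analysis | 30% v 50% | 40% v 60% |
|---|---|---|
| Log-rank | 83–85% | 83–85% |
| Mann–Whitney, unhealed tied last | 83% | 81–83% |
| Chi-square, healed or not | 83% | 83% |
| Mann–Whitney, healed only | 7% | 10% |

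**3. A second set of assumptions.** With 93 per arm, hazard ratio 1.6 and control healing of 30%, 50% and 70%:

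| Analysis | 30% | 50% | 70% |
|---|---|---|---|
| t test, healed only | 5% | 9% | 23% |
| Mann–Whitney, unhealed tied last | 46% | 65% | 75% |
| Log-rank | 48% | 67% | 82% |

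With about 9% lost to follow-up, the tied-rank test gives 49%, 63% and 70%, and log-rank 48%, 67% and 76%. The tied-rank test is close to log-rank at low healing rates and falls behind as healing becomes common.

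**4. Confirmation and exit, side by side.**

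- The assessments at weeks 4, 8 and 12 are 28 days apart, so on their own they cannot supply two visits across 2 weeks.
- Care appointments at most 3 days apart give at least 4 in any 14 days (14/3 = 4.7), so they can.
- If exit rule (d) means confirmed healing, the patient leaves after confirmation and the two sections agree. If it means first observed closure, the confirming visit comes after exit. The text does not say which.
- A closure first seen after day 84 − 14 = 70 cannot be confirmed across 14 days by day 84. At 30% v 50%, the share of healings after day 70 is [(0.7^(70/84) − 0.7) + (0.5^(70/84) − 0.5)]/0.8 = (0.043 + 0.061)/0.8 = 13%. Across all the assumed rates it is 8–14%.

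**The case against.** The strongest reply is that the list already contains workable tests. Mann–Whitney with every unhealed ulcer tied at the worst rank uses all patients and loses little power. Total healing is a separate aim, and chi-square on it would detect the same benefit with about 83% power. This stands. A reader might infer that the listed tests cannot handle open ulcers, or that the plan would miss a large benefit; the figures above do not support either. The fall to 7% belongs to a healed-only comparison, which the protocol does not state and which its intention-to-treat sentence points away from. However, worst-rank scoring is not specified either, and it does not properly handle patients lost before week 12.

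A reader might also infer that the rule that healing "is confirmed in two consecutive visits across 2 weeks" cannot be met under the trial's exit rule. That does not follow: appointments within 72 hours allow it if exit comes after confirmation. What remains is an ambiguity. The late-closure problem arises only if no visit after week 12 counts, which the protocol does not say, and any such cut-off falls on both arms alike.

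Finally, this is a condensed article and an SAP may exist. Covariates and event-dating rules could properly be left to it. But the article does more than stay silent: it gives an explicit list of methods, applies intention to treat and imputation to all analyses, and classes healing as a dropout. Those statements need correcting where they stand.

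**Conclusion.** The point holds in limited form. For a named secondary endpoint measured in days, with follow-up to week 12, the stated methods include none for censored times. Imputation is prescribed without separating censored from missing, and the endpoint event is classed as a dropout. Following the text can therefore exclude open ulcers or impute healing days for them, though it does not require either.

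The cost ranges from almost nothing (unhealed ulcers tied last, full follow-up) to nearly all the power (healed patients only: 7% against 83–85% at 30% v 50%). Which of these applies is left to the analyst. The figures rest on assumed healing rates, constant hazards and, at 102 per arm, no early loss. The healing definition and the exit rule are ambiguous but do not contradict each other outright. This should be corrected; it does not touch the primary endpoint.

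**What to change.** 1. Analyse time to healing in all randomised patients by Kaplan–Meier and log-rank, with a Cox model for treatment adjusted for baseline ulcer area.
2. Censor unhealed ulcers at their last assessment, and state that these times are not imputed.
3. Count healing as an event. In the analysis, keep it apart from the other three dropout criteria and outside the missing-data rule.
4. Date the event at the first of the two confirming visits.
5. Reconcile Secondary outcome measures with Intervention: state whether exit follows first or confirmed closure, which visits count towards confirmation, and how closures first seen after day 70 are counted.

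The cost is wording in the protocol or SAP. Items 1 to 4 need no new measurement, because wound area and healing days are already collected. Item 5 costs no more than wording unless the reconciled text calls for an extra contact to confirm late closures.
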